### Genomic Alterations in Primary Tumors Versus Metastases

An increasing number of studies have identified the existence of genetically distinct clonal subpopulations in some primary tumors [12]. Breast cancers have been classified by means of microarray-based comparative genome hybridization in single cells as either monogenomic or polygenomic, the latter having several clones that are evident in the primary tumor; polygenomic diagnoses carry a poorer prognosis [13,14]. Individual breast cancer tumor cell clones may harbor unique genetic alterations in addition to the founder mutations [15,16]. Distinct populations of breast cancer cells appear to interact in a competitive manner, both in the primary tumor and the micrometastatic environment. The selective pressure of therapeutic interventions can allow resistant cell clones to persist (usually as *dormant* cells) in distant organs. For unknown reasons these clones may expand, first in a silent way and later generating overt metastases, usually several years after the primary diagnosis. A substantial number of subdominant somatic mutations present in the primary tumor can evolve to become dominant in metastatic sites due to a selection process that is a consequence of the therapy [8,10]. Thus, the biology of metastases may be quite different from that of the primary tumor. This phenomenon can be particularly relevant in tumors that relapse after adjuvant treatments, especially if the relapse occurs years after the removal of the primary tumor.

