## Methods

### Study Design and Objectives

This is a multicenter, transversal, observational study performed by the Medical Oncology departments of three hospitals in Madrid, Spain: University Hospital Gregorio Marañón (UHGM), University Hospital Clínico San Carlos, and University Hospital Infanta Cristina. The primary objective of this study is to assess the concordance of mutations and other genomic findings between the primary tumor tissue and metastatic tissue in patients with MBC. Secondary objectives include determining the genomic profiles of CTCs and cfDNA from peripheral blood (liquid biopsy) and comparing these genomic profiles with those from the primary tumor and metastatic tissue for each patient, in order to assess the mutations in the genes of the signaling pathways that are relevant to the disease (ER/PR, HER2, PI3K/RAC-alpha serine/threonine-protein kinase [AKT1]/mTOR, and MAPK pathways, and CDK 4/6 activation) in the various tissues. Additionally, a final objective is to test the feasibility of introducing liquid biopsies as a translational laboratory tool in clinical practice.

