The genome sequencing data will be analyzed using bioinformatics tools. Sequencing reads will be aligned to the human reference genome building hg38 (GRCh38) to generate a list of potential genomic variations through variant-calling procedures. The alignments will be run using tools based on the Burrows-Wheeler Transform such as Burrows-Wheeler Aligner or Bowtie2. The aligned results will be processed using the SAMtools suite in order to obtain sorted, indexed, and binary files. If necessary, duplicate reads will be marked with Picard and removed before single nucleotide variation (SNV) identification with softwares such as SAMtools, mpileup, and MuTect. These programs will be used to detect low-frequency variants, as data cannot be expected to follow normal ploidy models. Additional steps will be performed if needed, such as the recalibration and realignment using BaseRecalibrator and IndelRealigner, both in the GATK suite. In recent years, a number of important algorithms and implementations have been designed for specific SNV detection tasks in matched samples. Depending on the number and nature of the detected SNVs, it may be appropriate to filter the results in order to keep only those located in exon junctions, or those leading to nonsynonymous changes. Moreover, germinal DNA will be taken as a control to assess background noise, and establish sample-specific thresholds for SNVs to be accepted. Identified and confirmed SNVs will be annotated with broadly-used tools such as SIFT, Variant Effect Predictor, or MutationAssessor. Finally, self-contained pathway and functional analyses will be applied to the obtained results, in order to check that a specific pathway has different genomic or expression patterns between compared samples. The high throughput sequencing raw data will be stored as clinical research files for further reevaluations. All reference genomic files containing the genes, transcripts, and annotated mutations will be used as the control genomic profile of each sample.

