## Discussion

The MIRROR study is one of the first observational studies to test the hypothesis that breast cancer metastases and primary tumors harbor different genomic profiles (related to genomic regions of interest) in a clinically relevant proportion of MBC patients, while concurrently assessing whether genomic aberrations found in the metastatic tissue are detectable in CTCs and cfDNA. Our study is a descriptive observational trial in the clinical setting. Genomic data will be described along with the clinical course of the disease for each patient. Therefore, data will include the type and the time of recurrence, and the different therapies received until the biological samples were collected.

Most registration trials examining new targeted agents involve companion diagnostic studies that are implemented in parallel with the efficacy study. In the majority of these studies, tumor biopsies are required prior to enrollment in order to characterize the genomic status of the patient. However, for practical reasons, some studies are accepting primary tumors as appropriate material for genomic testing. When biological samples of the current disease status are not available, two hypotheses have to be assumed: (1) all the genomic aberrations that are present in the metastases were already present in the primary tumor, and (2) all metastatic sites are genomically homogeneous. However, these hypotheses may not be true or, more precisely, they could be true in some patients but not in others. In this study, we intend to shed some light onto this issue.

The results of the present study may have a significant influence on the practical management of patients with MBC, and may guide clinicians towards a better stratification of patients, resulting in more effective and less toxic treatments. Additionally, if genomic mutations found in metastatic tissue are similar to those detected in CTCs and/or cfDNA, liquid biopsies could prove to be a more convenient, non-invasive, and easily accessible source of genomic material for the analysis of mutations and other genomic aberrations in MBC.

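### SNVs are accepted sample by sample with no stated re-read in the paired tissue, and the SNV filter depends on the results, so primary–metastasis concordance can be distorted for low-fraction variants

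*Protocol article*

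**What the plan says.** All references are to the protocol article.

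- **Objective and hypothesis.** Study Design and Objectives: "The primary objective of this study is to assess the concordance of mutations and other genomic findings between the primary tumor tissue and metastatic tissue". The Discussion gives the hypothesis that "breast cancer metastases and primary tumors harbor different genomic profiles" in a clinically relevant share of patients.
- **Acceptance of SNVs.** Sample Size and Statistical Analyses: germline DNA serves as the noise control and is used to "establish sample-specific thresholds for SNVs to be accepted". On the variant callers, the same section adds: "These programs will be used to detect low-frequency variants".
- **Matched samples.** The section notes that "a number of important algorithms and implementations have been designed for specific SNV detection tasks in matched samples", without committing to use any of them for the primary–metastasis pair. The scoring algorithm it promises compares cfDNA and CTC-DNA with the tissues and the germline; it does not cover primary against metastasis.
- **Filter.** "Depending on the number and nature of the detected SNVs, it may be appropriate to filter the results", keeping only SNVs at exon junctions or those with nonsynonymous effect.
- **Expected biology.** Genomic Alterations in Primary Tumors Versus Metastases: "A substantial number of subdominant somatic mutations present in the primary tumor can evolve to become dominant in metastatic sites".
- **Timing.** According to Results, no sample has yet been extracted or sequenced. Raw sequencing data will be kept for re-evaluation.

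**The concern.** Concordance is a property of a pair of samples, but the stated acceptance rule works on one sample at a time. A variant present in both tissues can pass in one and fail in the other because of tumor content, effective depth or a low clonal fraction. If the two accepted lists are then compared, that variant appears as a difference between the tumors.

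The variants exposed to this are the ones the study cares about. The Introduction expects mutations that are minor in the primary and dominant in the metastasis, and the callers are chosen to find low-frequency variants. Missing such a mutation in the primary would make clonal selection look like a new mutation. Sample quality may also differ within a pair: more than 70% cellularity is an aim of area selection (Biobanking and Sample Analysis), and Results expects some tissue to be unusable.

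The results-dependent filter adds a second route. The set of SNVs on which concordance is computed can be chosen after the SNVs have been seen.

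**Working it through.** **1. The plan's own figure.** The only calculation in the article is the detectable effect of 1.29 at 80% power, with depth 3000x, coefficient of variation 0.4 and 40 patients. For counts in two groups, n per group = 2(z_α/2 + z_β)²(1/depth + CV²)/(ln effect)². With two-sided α = 0.05 (assumed; not stated), this is 2 × 7.849 × (1/3000 + 0.16)/(ln 1.29)² = 38.8, so 39 per group. With 40 per group the detectable effect is 1.285 and power for 1.29 is 81.2%. The figure reproduces, but it concerns a fold-change in counts and says nothing about the accuracy of concordance.

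**2. Shared mutations under independent calling.** Let s₁ and s₂ be the probabilities of calling a truly shared mutation in each tissue. Among those called at least once, the share that looks discordant is 1 − s₁s₂/[1 − (1 − s₁)(1 − s₂)], which is 2(1 − s)/(2 − s) when s₁ = s₂ = s. True discordance is 0% throughout; all s values are assumptions.

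| s₁ | s₂ | Looks discordant |
|---|---|---|
| 0.99 | 0.99 | 2.0% |
| 0.95 | 0.95 | 0.10/1.05 = 9.5% |
| 0.90 | 0.90 | 0.20/1.10 = 18.2% |
| 0.80 | 0.80 | 0.40/1.20 = 33.3% |
| 0.95 | 0.80 | 23.2% |

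**3. Which variants are affected.** Here s is the binomial probability of reaching the threshold at a given depth and variant allele fraction (VAF). Thresholds, VAFs and the 300x effective depth are assumptions; 3000x is the article's depth.

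| Depth | VAF in both tissues | Thresholds | Looks discordant |
|---|---|---|---|
| 3000x | 35% or 10% | any pair tried, 1% to 5% | about 0% |
| 3000x | 3% | 1% and 2% | about 0% |
| 3000x | 3% | 1% and 3% | 48.5% |
| 300x | 3% | 1% and 2% | 11.7% |
| 300x | 3% | 2% and 2% | 20.2% |

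The 35% row stands for a clonal heterozygous variant at 70% tumor content (0.70/2, assuming no copy-number change). The last row has a common threshold and still gives false discordance, so independent calling is the cause.

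**4. Net direction.** Let d be the true share of private mutations, detected with probability s_p. Observed discordance is [d·s_p + (1 − d)·2s(1 − s)]/[d·s_p + (1 − d)(2s − s²)].

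- d = 0.30, s = s_p = 0.90: (0.270 + 0.126)/(0.270 + 0.693) = 0.411, above the truth.
- d = 0.30, s = 0.95, s_p = 0.50: (0.150 + 0.0665)/(0.150 + 0.698) = 0.255, below the truth.

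Observed discordance exceeds d when s_p > (2s − s²) − 2s(1 − s)/d. At d = 0.30 the direction therefore reverses only if s_p falls below 0.9975 − 0.095/0.30 = 0.68 (s = 0.95) or 0.99 − 0.18/0.30 = 0.39 (s = 0.90). At s = 0.80 the bound is negative, so it cannot reverse. With s_p = s, observed discordance is always too high when s is below 1.

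**5. Effect of a paired re-read.** At 3000x and VAF 3%, looking up a known locus at 0.5% (15 reads) misses about 0% of shared variants.

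**The case against.** The strongest reply is that the article never says an SNV accepted in only one tissue counts as discordant. It is a condensed account, and the classification may be in a full protocol or SAP that is not shown. That stands, and it is why the step from acceptance to discordance is given here as an inference. What does not depend on it is the stated text: a per-sample acceptance rule, matched-sample methods mentioned without commitment, and a filter that depends on the results.

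Three further replies also hold in part.

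- Thresholds set from germline noise remove artefacts that would otherwise look like private mutations. A reader might infer that the sample-specific cut is itself the fault; step 3 shows that a common cut has the same problem.
- A reader might infer that missed calls can only create discordance. That is true for shared mutations; missing a private one removes a discordant item, and step 4 shows the net error can reverse.
- A clone that moves from minor to dominant is a real difference between the tissues. But a change in fraction is a different finding from a mutation absent in the primary, and independent calling can confuse the two.

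The analyses are labelled exploratory and the raw data are kept, so a later re-analysis would be possible. This lowers the urgency. It does not remove error from the primary result, which the Discussion says may influence patient management.

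**Conclusion.** The concern holds in a limited form. As stated, the sequencing analysis can accept a shared low-fraction SNV in one tissue and reject it in the pair, with no re-read to separate absent from undetected, and the filter can be chosen after the SNVs are seen. If the accepted lists are what is compared, 9.5% to 33% of truly shared mutations called at least once would look discordant at assumed detection probabilities of 0.95 to 0.80. The error is confined to variants near the cut or samples with low effective depth. For clonal variants at 3000x it is about 0%. The usual direction is toward the study's hypothesis, but this is not guaranteed.

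A reader might go on to a rate of patients with identical tumors labelled discordant. The documents do not support one: it would need a number of shared mutations per patient, a detection probability, and a rule that one mismatch makes a patient discordant. None of these is stated.

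**What to change.** Before sequencing starts:

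1. **Paired re-read.** For any SNV accepted in one of a patient's tumor-derived samples (primary, metastasis, cfDNA, CTC-DNA), re-read that locus in the patient's other tumor-derived samples. Score it present if the reads exceed a cut set from the germline or local error rate. Score it absent only if depth gives a pre-set probability, for instance 95%, of seeing a pre-set allele fraction. Otherwise score it not evaluable, leave it out of the denominator and report the count. As an illustration with the assumed values above, a 300x site has a 99.4% chance of showing a 3% variant at a 1% cut but 88.8% at a 2% cut, so only the first would be evaluable.
2. **Filter.** Fix the nonsynonymous and exon-junction filter now, and report the unfiltered concordance as a sensitivity analysis.
3. **Both versions.** Report concordance under independent calling beside the paired result.

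The cost is protocol wording and some bioinformatics work on the same reads; no new samples are needed. There are two downsides. Some loci become not evaluable. A re-read that is more lenient than the first call can also score noise as present, which pushes toward concordance. That is why its cut must come from the error rate and why both versions should be shown.

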## Results

Patient recruitment started in November, 2013 and is currently ongoing. To date, 41 patients have a complete set of tissue samples available (plasma, CTCs, and FFPE of primary tumor and metastatic tumor). However, none of these samples have undergone nucleic acids extraction or targeted deep sequencing. Due to the high standards of the quantity and quality of DNA required to perform these procedures, the recruitment period is still open (it is expected that some of the tissue samples will not be valid). Final study results are expected to be available in December, 2016. Additional information regarding the progress of this study is described in the Figure 1.

**Figure 1 figure1:**
[figure not shown]
Flowchart of participants, specimens, and samples through the study.

## Discussion

The MIRROR study is one of the first observational studies to test the hypothesis that breast cancer metastases and primary tumors harbor different genomic profiles (related to genomic regions of interest) in a clinically relevant proportion of MBC patients, while concurrently assessing whether genomic aberrations found in the metastatic tissue are detectable in CTCs and cfDNA. Our study is a descriptive observational trial in the clinical setting. Genomic data will be described along with the clinical course of the disease for each patient. Therefore, data will include the type and the time of recurrence, and the different therapies received until the biological samples were collected.

Most registration trials examining new targeted agents involve companion diagnostic studies that are implemented in parallel with the efficacy study. In the majority of these studies, tumor biopsies are required prior to enrollment in order to characterize the genomic status of the patient. However, for practical reasons, some studies are accepting primary tumors as appropriate material for genomic testing. When biological samples of the current disease status are not available, two hypotheses have to be assumed: (1) all the genomic aberrations that are present in the metastases were already present in the primary tumor, and (2) all metastatic sites are genomically homogeneous. However, these hypotheses may not be true or, more precisely, they could be true in some patients but not in others. In this study, we intend to shed some light onto this issue.

The results of the present study may have a significant influence on the practical management of patients with MBC, and may guide clinicians towards a better stratification of patients, resulting in more effective and less toxic treatments. Additionally, if genomic mutations found in metastatic tissue are similar to those detected in CTCs and/or cfDNA, liquid biopsies could prove to be a more convenient, non-invasive, and easily accessible source of genomic material for the analysis of mutations and other genomic aberrations in MBC.

## Abbreviations

AE: adverse event
AKT1: RAC-alpha serine/threonine-protein kinase
CDK: cyclin-dependent kinase
cfDNA: circulating free DNA
CNV: copy number variation
CSC: cancer stem cell
CTCs: circulating tumor cells
ER: estrogen receptor
FFPE: formalin-fixed paraffin-embedded
HER2: human epidermal growth factor receptor 2
MBC: metastatic breast cancer
mTOR: mammalian target of rapamycin
PI3K: phosphoinositide-3-kinase
PR: progesterone receptor
SNV: single nucleotide variation
UHGM: University Hospital Gregorio Marañón
WBC: white blood cell
